### Participants

Fifty consecutive patients with suspected systemic autoimmune/autoinflammatory response or ASIA syndrome will be recruited from one of the five aforementioned departments. In the present study, patients are considered to have ASIA when at least three major criteria from Table 1 are present, as previously published [17]. Only referrals from the outpatient ASIA clinics will be accepted and no active recruitment will be undertaken. Subjects will be eligible for inclusion if they meet all of the following criteria:- Patients >18 years of age and written informed consent obtained;- Suspected ASIA syndrome after elective inguinal hernia, POP, or SUI repair, defined as at least three major ASIA criteria (Table 1), of which the exposure to an external stimulus (PP mesh) is one;- ASIA complaints started specifically after the implantation of PP mesh and were not present before the surgical repair.

**TABLE 1 T1:** Diagnostic criteria autoimmune/autoinflammatory syndrome induced by adjuvants (ASIA) syndrome [17].

Major criteria
- Removal of inciting agent induces improvement
- Exposure to an external stimulus (infection, vaccine, silicone, adjuvant) prior to clinical manifestations
- The appearance of ‘typical’ clinical manifestations:
- Myalgia, myositis or muscle weakness
- Arthralgia and/or arthritis
- Chronic fatigue, unrefreshing sleep or sleep disturbances
- Neurological manifestations (especially associated with demyelination)
- Cognitive impairment, memory loss
- Pyrexia
- Sicca (dry mouth and/or dry eyes)
- Typical biopsy of involved organs
Minor criteria
- The appearance of autoantibodies or antibodies directed at the suspected adjuvant
- Other clinical manifestations (e.g., irritable bowel syndrome)
- Specific HLA (e.g., HLA DRB1, HLA DQB1)
- Evolvement of an autoimmune disease (e.g., multiple sclerosis, systemic sclerosis)

Patients will be excluded from participation in this study if one or more of the following is present:- Known autoimmune/inflammatory disorders;- Known malignancies;- (Low grade) infections or other inflammatory diseases at time of surgery;- Cognitively impaired individuals.- Recent (<3 months) vaccination

Sample size calculation is not applicable as the present study is a pilot and preceding literature about the validity of MAT is absent, but considering the low expected number of cases annually, with strict inclusion criteria (at least 3 major ASIA criteria present), and no active recruitment in only three centres, total number of proposed inclusions has been estimated restrictively, in order not to misjudge availability of inclusions.

### Interventions

After inclusion, patients will be asked to fill out several questionnaires and to visit the immunology outpatient clinic (T0) to undergo a MAT and blood testing. For the MAT, 1 mL methyl ethyl ketone (MEK) is used to dissolve a 5 cm^2^ mesh for at least 48h, to max 72 h. 25 μL of the MEK solution and part of the mesh are tested topically in a Finn chamber. MAT is considered positive when a dermal reaction on the topical applicant occurs within 48 h, as assessed by an immunologist in Máxima MC or MUMC+.

At first visit, blood samples from all subjects will be obtained as standard diagnostic immunologic tests in which the following will be determined: C-reactive protein (CRP), haemoglobin, erythrocyte sedimentation rate (ESR), leukocytes, differentiation of leukocytes (including eosinophil count), thrombocyte count, creatinine, creatine kinase (CK), albumin, alanine transaminase (ALT), ANA, anti-dsDNA, ANCA, Rheumatoid factor (Rf), anti-CCP, and if indicated total level of protein, interleukin-6 (IL-6), total IgG and subclasses. Additionally, an extra blood sample will be obtained for diagnostic purposes to exclude specific systemic or autoimmune diseases if any of the determinations is abnormal.

Patients will be asked to fill out a set of questionnaires to assess subjective complaints, changes of complaints over time and changes related to mesh removal (if applicable). The Patient Global Impression of Improvement (PGI-I), Pain Catastrophizing Scale (PCS), Hospital Anxiety and Depression Scale (HADS), Short Form Health Survey (SF-12), and the Connective Tissue Disease Screening Questionnaire (CSQ) will be obtained. Patients are asked to complete these at T0, T1 and T2. In case of mesh removal, T1 and T2 will be respectively 6 and 12 months after mesh removal. All patients, independent of MAT and blood sample outcomes or spontaneous resolution of systemic complaints, will be followed up in the first year after inclusion.

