**Discussion:**

Current evidence on a causal relation between polypropylene mesh and ASIA syndrome is lacking. In this study, mesh allergy testing will be evaluated as a potential first objective screening test for inflammation-like response specific to polypropylene, in patients meeting diagnostic criteria for ASIA syndrome following polypropylene implantation. This study will be performed to add to existing literature on ASIA with polypropylene adjuvants and to help reduce knowledge gaps on diagnosis and prognosis.

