### Outcomes

Primary outcome is the value of MAT as an objective diagnostic test for patients who fit the current ASIA criteria. Secondary outcomes include the value of immunologic blood tests, and the association between both subjective outcomes (autoimmune/autoinflammatory symptoms) and objective findings (MAT, blood test).

Another secondary outcome is the success rate of (partial) mesh removal for the resolution of subjective complaints. This success rate is defined as a complete resolution of subjective complaints (on CSQ) and ASIA symptoms (Table 1) and the report of a “much better” or “very much better” condition on PGI-I.

Baseline and dynamic patient demographics will be collected, including age, gender, ASA classification (American Society of Anaesthesiologists), year of PP implantation and type of PP implant, duration of ASIA complaints, pain scores (using Numerical Rating Scale; NRS), body mass index (BMI) smoking status, medication use (including immunosuppressants), previous imaging, time of resolution of symptoms, and remaining symptoms.

Additionally, in case of surgical mesh removal, the following parameters will be collected: intraoperative macroscopic configuration of mesh, duration of surgery, additionally performed neurectomy, and complications. All explanted meshes will be examined histopathologically to check for granulomatous inflammatory or acute inflammatory reactions surrounding the explant.

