### Limitations

MAT is used to test for type IV allergic reactions as a possible underlying mechanism for systemic complaints. There is no literature regarding this mechanism so far, and the effectiveness and meaning of the MAT for ASIA patients is uncertain. The proportion of patients that present with all symptoms supporting presence of ASIA as stated by Shoenfeld’s criteria, but with a negative MAT is yet to be deduced [17]. Furthermore, as this pilot is not a clinical trial and treatment is not randomized, it is likely that patients with complaints will opt for surgical removal of the PP implant, making it increasingly difficult to illustrate the normal progression of ASIA symptoms. Note should be taken that the effectivity of surgical removal is not the primary aim of this pilot! The natural course of complaints of ASIA patients will be displayed for future studies to further base new standards of care on.

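### MAT is described as specific to polypropylene, but its single result covers MEK solution and mesh together, so a positive cannot be attributed to polypropylene

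*Protocol article*

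**What the plan says.** Four parts of the protocol article bear on this.

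- **Claim.** The Discussion paragraph of the abstract says MAT will be evaluated as a "a potential first objective screening test for inflammation-like response specific to polypropylene".
- **Preparation and application.** Under Methods, Interventions, "1 mL methyl ethyl ketone (MEK) is used to dissolve a 5 cm^2^ mesh for at least 48h, to max 72 h". Then 25 μL "of the MEK solution and part of the mesh are tested topically in a Finn chamber".
- **Scoring.** The same section gives one rule: "MAT is considered positive when a dermal reaction on the topical applicant occurs within 48 h", as judged by an immunologist. No separate reading of the solution and the mesh piece is described.
- **Use.** Under Outcomes, the value of MAT is the primary outcome. Under Statistical Methods it is summarised as the percentage of positive tests, and the objective findings, MAT among them, are dichotomised for the association with the number of complaints.

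Outcomes also lists "year of PP implantation and type of PP implant" among the data collected. The Discussion plans to relate histopathology of explanted meshes to positive MAT results, and says MAT is meant to help physicians decide about treatment, mesh removal included.

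**The concern.** The stated property of the test and its stated procedure do not match. A result specific to polypropylene has to be positive because of polypropylene. The result defined here is positive for a skin reaction to anything in a mixed applicant: the solvent, a substance taken up by the solvent, the mesh, or local irritation from any of these. The rule contains nothing that separates them.

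The primary outcome is at stake. The study will report a percentage, and with the abstract's wording beside it readers will take it as the share of these patients who react to polypropylene. As described, it is the share who react to one preparation. The same ambiguity passes into the association analysis and the planned comparison with histopathology, because both use the same dichotomised result. The study aims to clarify whether an implant material provokes an immune response, so what a positive test is positive for matters.

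**Working it through.** The article gives no expected MAT rate and no sample size calculation, so there is no figure of its own to reproduce. The main check is a comparison of the text; the arithmetic only illustrates scale.

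**Step 1: what can cause a positive, as written.** The applicant has two parts, MEK solution and a piece of mesh. The rule accepts any dermal reaction on the applicant within 48 h.

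| Source of reaction | Scored positive? | Evidence about polypropylene? |
|---|---|---|
| Mesh material itself | Yes | Yes, if the mesh is polypropylene, as the context implies |
| MEK | Yes | No |
| Another substance taken up in the solution | Yes | No |
| Local irritation by the applicant | Yes | No |

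All four rows give the same recorded value. The claim in the abstract needs the first row to be distinguishable from the other three, and it is not.

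**Step 2: what the solution contains.** The Interventions section says MEK "is used to dissolve a 5 cm^2^ mesh for at least 48h, to max 72 h", and then has part of the mesh applied as a solid. Either the mesh does not fully dissolve or the solid piece comes from elsewhere. The article does not say which, so the content of the liquid is undefined on its own wording. No outside chemistry is needed for this.

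**Step 3: what a negative means.** A negative says that neither the solution nor the mesh piece produced a reaction within 48 h. Since a piece of mesh was on the skin, this carries some information about contact reaction to that material. The attribution problem therefore lies with positives.

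**Step 4: scale, for illustration.** Inputs: n = 50 (Participants); r = the proportion of patients whose applicant reacts for a reason other than polypropylene. The documents do not give r; a range of 1% to 10% is assumed.

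- Expected number of such positives: 50 × r
- Probability of at least one: 1 − (1 − r)^50
- Probability of at least five: upper binomial tail, n = 50

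| Assumed r | Expected number | P(at least 1) | P(at least 5) |
|---|---|---|---|
| 1% | 0.5 | 0.395 | 0.0001 |
| 2% | 1.0 | 0.636 | 0.003 |
| 5% | 2.5 | 0.923 | 0.104 |
| 10% | 5.0 | 0.995 | 0.569 |

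As an example, 5 positives out of 50 would be reported as 10%, with an exact 95% interval of 3.3% to 21.8%. With r at 10%, five or more positives would arise more often than not with no response to polypropylene at all. With r at 1%, that would be almost impossible. The single combined result gives no means of telling which situation applies.

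**The case against.** The strongest reply is that the abstract makes no settled claim. It calls MAT a potential test to be evaluated. The Discussion says MAT has not been validated for this use and calls the study exploratory, and Limitations says its effectiveness and meaning in these patients are uncertain. This stands as far as it goes: the authors do not oversell MAT's usefulness. But these caveats concern whether a contact reaction has anything to do with ASIA. Limitations states that "MAT is used to test for type IV allergic reactions as a possible underlying mechanism for systemic complaints" and questions that mechanism; it does not say that the reacting substance is unidentified. The word potential in the abstract qualifies the screening role, not what the response is said to be specific to.

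Three stronger readings are tempting, and the documents do not support them.

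- **That the test mesh is not the patient's own product.** The article does not name the mesh or say whether it matches the implant. It is a condensed account, and the full protocol may specify product, matching and any solvent-only patch. Silence here is not an error, and the documents give no basis for estimating how many patients would be unmatched.
- **That the liquid holds only additives because polypropylene does not dissolve in MEK.** Nothing in the article establishes this. The point rests on the shared result, whatever the liquid contains.
- **That a negative is uninformative too.** Step 3 of the working shows otherwise.

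It would also be wrong to insist that each patient be tested with the implanted product. A common mesh addresses the shared material and a matched mesh addresses the patient's own implant. Those are different questions, and the choice between them is a trade-off.

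**Conclusion.** The concern holds in a limited form. As described in Interventions, a positive MAT cannot be attributed to polypropylene rather than to the solvent solution or a substance in it. The primary percentage therefore measures contact reactivity to the preparation used, and the specificity stated in the abstract is not a property of the test as described. This follows from the article's own wording and needs no outside source.

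The numerical effect cannot be fixed from the documents. Under the assumed 1% to 10% rate of unrelated reactions, 0.5 to 5 of 50 results would be affected. That matters most if few tests are positive, because such reactions could then make up much of the numerator.

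The finding does not invalidate the pilot. The combined percentage remains a legitimate description of what was observed. What needs to change is how it is broken down and what is claimed for it.

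**What to change.** 1. **Interventions.** Apply and read the MEK solution and the mesh piece in separate chambers. Report each result, and a combined result that is positive if either chamber is. Enrolment is under way, so patients already tested may have only the joint result; state how many were tested under each arrangement.
2. **Statistical Methods.** Tabulate MAT positivity by the implant type already collected under Outcomes, as description only.
3. **Abstract, Discussion paragraph.** Replace the claim of specificity to polypropylene with a response to mesh material and its MEK extract.

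Separate chambers show which part of the applicant provoked a reaction. They do not separate MEK from what it has taken up, so the rewording is needed even if the chambers are split.

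The cost is one additional chamber on the same patch, one additional table and a narrower claim. The table and the rewording cost almost nothing.

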### Outcomes

Primary outcome is the value of MAT as an objective diagnostic test for patients who fit the current ASIA criteria. Secondary outcomes include the value of immunologic blood tests, and the association between both subjective outcomes (autoimmune/autoinflammatory symptoms) and objective findings (MAT, blood test).

Another secondary outcome is the success rate of (partial) mesh removal for the resolution of subjective complaints. This success rate is defined as a complete resolution of subjective complaints (on CSQ) and ASIA symptoms (Table 1) and the report of a “much better” or “very much better” condition on PGI-I.

Baseline and dynamic patient demographics will be collected, including age, gender, ASA classification (American Society of Anaesthesiologists), year of PP implantation and type of PP implant, duration of ASIA complaints, pain scores (using Numerical Rating Scale; NRS), body mass index (BMI) smoking status, medication use (including immunosuppressants), previous imaging, time of resolution of symptoms, and remaining symptoms.

Additionally, in case of surgical mesh removal, the following parameters will be collected: intraoperative macroscopic configuration of mesh, duration of surgery, additionally performed neurectomy, and complications. All explanted meshes will be examined histopathologically to check for granulomatous inflammatory or acute inflammatory reactions surrounding the explant.

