## Abstract

**Background:**

An increasingly vocal movement of patients with systemic complaints, supposedly linked to polypropylene mesh implants, is leading to increasing numbers of patient-preferred mesh-less surgical repairs for inguinal hernia, stress urinary incontinence, and pelvic organ prolapse. However, current literature does not support any association between polypropylene implants and Autoimmune Syndrome Induced by Adjuvants (ASIA). This prospective pilot aims to examine autoimmunity in patients in whom ASIA is suspected, based on previously described criteria. We aim to demonstrate the effectiveness of mesh allergy testing and to investigate the natural evolvement of ASIA symptoms or the effect of mesh removal on ASIA complaints.

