### Statistical Methods

Baseline patient demographics will be presented as descriptive statistics. Primary outcome (rate of positive diagnostic tests) will be presented as descriptive statistics (percentage of positive tests) at all predefined time points.

Secondary outcomes include the association between subjective (questionnaire outcomes evaluating systemic symptoms or ASIA symptoms) and objective findings (MAT, blood test). For this outcome, subjective complaints are summed (each complaint is 1 point). Objective findings are dichotomized. The association between the number of subjective complaints and the presence of objective findings is subsequently calculated via Chi-Square Test or Fisher’s Exact Test in low expected counts, where applicable. For missing data, percentage of data present will be described. If known, a rationale for missing data will be presented. If only limited data is missing per variable, analysis will proceed as expected. Imputation of missing data is not preferred as imputation within the relatively small sample size would decrease validity of the study, as well as the intention to present real data as it is.

A p-value <0.05 is considered statistically significant. Success rates of (partial) mesh removal will be presented as descriptive statistics (percentage of successful surgery).

Patients are considered to have ASIA when either two major or one major and two minor criteria are present (adapted from Cohen Tervaert 2018) [17]. In the present study, we only considered patients to have ASIA when at least three major criteria are present.

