This pilot aims to assess the diagnostic value of Mesh Allergy Testing as a first objective screening tool, to aid physicians in decision-making for possible treatments (including high-risk mesh removal) [26, 27]. MAT has not been validated as a test for screening systemic reaction to an adjuvant before, necessitating the current exploratory nature of this study. While findings in physical examination and medical history can aid in a differential diagnosis, testing patients for susceptible HLA-types or antibodies related to mesh has unknown predictive values. Currently, only subjective patient or observer described diagnostic modalities are considered in the ASIA criteria, leading to a lack of specificity in discerning patients with ASIA from other syndromes (Table 1) [17]. The current pilot therefore intentionally opposes earlier case series on ASIA by only including patients with at least three major ASIA criteria, to form a narrower but more specific patient population. Consequently, to assess the value of MAT, patients who suffer from light ASIA symptoms or who only slightly match the diagnosis, will be excluded to create a homogeneous population of patients who fit the criteria of ASIA most optimally, to test value of MAT [32]. In addition, patients will be referred to an immunologist to test for identifiable autoimmune diseases and relevant confounders, and to exclude other illnesses that could correctly explain the presented symptoms.

In our pilot, the explanted meshes will all be sent for histopathologic examination to identify ongoing microscopic inflammatory processes and to relate these to potentially positive MAT results, despite earlier research by Fadaee et al. (2019) showing minor to no benefits of this test as proof of any relation between PP and ASIA [33]. Additionally, while presence of (chronic) inflammation, foreign body reaction, and fibrosis surrounding the mesh explant are to be expected, reports of pathology findings can lead to a deeper understanding of the difference between autoimmunity and (normal) foreign body reactions in patients suffering from ASIA [33]. Objective diagnostic modalities for ASIA are essential, and a rapid, low-cost, non-invasive diagnostic test such as MAT could be a vast improvement in the diagnosis of patients; if results are promising and consistent [32].

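### The primary outcome is the diagnostic value of MAT, but only patients who meet the case definition are tested and only a positivity percentage is computed, so no result can show diagnostic value

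*Protocol article*

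**What the plan says.** The protocol article describes the primary outcome in two ways. Outcomes says: "Primary outcome is the value of MAT as an objective diagnostic test for patients who fit the current ASIA criteria". Statistical Methods says: "Primary outcome (rate of positive diagnostic tests) will be presented as descriptive statistics (percentage of positive tests) at all predefined time points".

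The stated ambition follows the first description. The Background of the Abstract says: "We aim to demonstrate the effectiveness of mesh allergy testing". The Discussion wants the diagnostic value of MAT as a screening tool assessed in order "to aid physicians in decision-making for possible treatments (including high-risk mesh removal").

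On who is tested, Participants says: "Fifty consecutive patients with suspected systemic autoimmune/autoinflammatory response or ASIA syndrome will be recruited". Entry requires at least three major criteria from Table 1. Statistical Methods uses the same threshold as the case definition: "we only considered patients to have ASIA when at least three major criteria are present". The Discussion adds that "patients who suffer from light ASIA symptoms or who only slightly match the diagnosis, will be excluded to create a homogeneous population". Under Interventions, MAT is performed in these included patients at T0.

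**The concern.** Diagnostic value means discrimination: the test has to behave differently in people with and without the condition. A positivity percentage among cases describes only one side of that comparison. If mesh carriers without complaints, or patients with similar complaints from another cause, reacted to MAT equally often, the study would report exactly the same primary result.

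The article links MAT to decisions about mesh removal, which it calls high-risk, and it warns elsewhere against operations without proper support. A percentage published under an outcome labelled diagnostic value could be read as support for using the test in that way, and the data could not bear that reading.

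**Working it through.** **Plan's own figure.** There is none to reproduce. Participants states that a sample size calculation does not apply, and 50 is a feasibility number. No test or precision target is attached to the primary outcome.

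**Step 1: what is estimable.**
- Positivity in cases, s: estimable, because all 50 patients are cases by the study's definition.
- False-positive rate in non-cases, f = 1 − specificity: not estimable, because no non-case is scheduled for MAT. The naturalistic comparison group in Study Design and the Discussion consists of unoperated participants. They are also cases, and that comparison concerns mesh removal.
- Within-case contrast is reduced further, because mild and borderline presentations are deliberately left out.
- The immunology work-up may reveal another disease after inclusion, but no MAT comparison with such patients is described.

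**Step 2: precision of the one estimable quantity.** Exact (Clopper-Pearson) 95% intervals with n = 50:
- 0/50 = 0%: 0% to 7.1%
- 5/50 = 10%: 3.3% to 21.8%
- 15/50 = 30%: 17.9% to 44.6%
- 25/50 = 50%: 35.5% to 64.5%
- 40/50 = 80%: 66.3% to 90.0%

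**Step 3: what a given rate implies for discrimination.** LR+ = s/f, LR− = (1 − s)/(1 − f), Youden J = s − f. Take s = 0.30 as an example. The values of f are assumptions, because the article supplies none.

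| Assumed specificity | f | LR+ | LR− | J |
|---|---|---|---|---|
| 99% | 0.01 | 0.30/0.01 = 30 | 0.70/0.99 = 0.71 | 0.29 |
| 95% | 0.05 | 0.30/0.05 = 6.0 | 0.70/0.95 = 0.74 | 0.25 |
| 90% | 0.10 | 0.30/0.10 = 3.0 | 0.70/0.90 = 0.78 | 0.20 |
| 70% | 0.30 | 0.30/0.30 = 1.0 | 0.70/0.70 = 1.0 | 0.00 |
| 50% | 0.50 | 0.30/0.50 = 0.6 | 0.70/0.50 = 1.4 | −0.20 |

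The same 30% fits an informative test, an uninformative one and one that points the wrong way. A high rate does not escape this. At 80% positive, LR+ is 0.80/0.05 = 16 if f = 0.05 and 0.80/0.50 = 1.6 if f = 0.50.

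**Step 4: does more data help?** No. A larger case series narrows the interval for s but adds nothing on f.

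**Step 5: other analyses involving MAT.** Statistical Methods relates complaint count to dichotomised findings by chi-square or Fisher's exact test. The Discussion plans to relate explant histopathology to MAT results. Both lie within cases, so neither gives specificity for ASIA.

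**The case against.** The strongest defence is that this is an exploratory pilot and says so. Statistical Methods already defines the primary outcome as a rate. The Discussion and Limitations concede that MAT is unvalidated and that its meaning in ASIA patients is uncertain. Limitations also presents the share of criteria-positive patients with a negative MAT as an open question. All of this is true, and it shows that the repair is small. It does not remove the fault. The caveats never mention the missing non-ASIA comparator, and the Outcomes, Abstract and Discussion wording still promises more than a rate. Pilot status excuses the absent sample size calculation, but not a primary outcome that the design cannot estimate. Nor could an analysis plan not shown here recover specificity from a case-only sample.

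Second, the design is informative in one direction. With 0/50 positive, the upper limit for sensitivity against the entry criteria is 7.1%, which would count heavily against MAT as a screening test in this population. That stands. It would be wrong to call the primary result worthless.

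Third, a reader might infer that MAT is never related to what happens after removal and that those data go unanalysed. The article does not support this. The questionnaire association is not restricted to T0, and in operated patients T1 and T2 fall 6 and 12 months after removal. The histopathology comparison also uses data from removal. What is not named is an analysis of MAT against the composite removal success defined in Outcomes. In a condensed article, leaving one exploratory table unlisted is not an error.

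**Conclusion.** The point holds for the primary outcome as worded. The study can estimate how often MAT is positive among patients with at least three major criteria, with an exact 95% interval of about 18% to 45% if 30% are positive. It cannot estimate diagnostic value: at that rate LR+ runs from 6.0 to 1.0 as the assumed specificity falls from 95% to 70%. The 30% rate and the specificities are illustrations. The conclusion does not depend on them, because it follows from the absence of any tested non-case.

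A reader might also infer that the investigators will report a high rate as proof of diagnostic value. The article does not say so, and several of its passages are cautious. The established fault is narrower: the named outcome and the planned estimate are different quantities, and the stated aims rest on the one that cannot be estimated. This should be corrected before analysis, and the article gives its stage as enrolment.

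**What to change.** 1. In Outcomes, restate the primary outcome as the proportion of included patients (at least three major criteria) with a positive MAT at T0, with an exact 95% CI. Statistical Methods reports positivity at all predefined time points, and the Introduction foresees testing after removal on indication. Keep any such later MAT results as secondary.
2. In the Abstract, Outcomes and Discussion, remove diagnostic value, effectiveness and suitability for screening as conclusions that this study can support.
3. In Limitations, state that no people without ASIA are tested, so the false-positive rate of MAT remains unknown.
4. Optionally, add an exploratory cross-table of T0 MAT by removal success at T2 in operated patients, and by spontaneous resolution in unoperated patients, with exact CIs. State that removal is self-selected and that cells may be small, since success requires complete resolution of complaints. Do not present the result as validated predictive value.

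The first three items change wording and add one interval. The fourth uses data already collected. The price is a narrower headline claim. Keeping the diagnostic claim would instead require the same MAT in people without ASIA, which is a different design.
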